**Exclusion Criteria:**

1. Subject with evidence of IgG antibodies against PfMSP-119 and PfF2 as measured by ELISA
  2. Subject with prior history of immunisation with Hepatitis B vaccine
  3. Subject with known history of malaria
  4. Subject with history of allergic reactions, hypersensitivity or anaphylaxis to any of the components of the study vaccines (JAIVAC-1 – Montanide ISA 720 malaria vaccine or Hepatitis B vaccine) (including adjuvant or peptide) or with history of serious allergic reactions to any substance, requiring hospitalisation or emergency medical care
  5. Subject with previous vaccination with any other malaria candidate vaccines
  6. Subject with use of an investigational or non-registered drug or vaccine other than the study vaccines within three (3) months preceding the first study vaccination, or planned use during the entire clinical trial period
  7. Subject, who receives any vaccination or gamma globulin during the three-month period prior to the first vaccination
  8. Subject with chronic administration (defined as more than 14 days) of immuno-suppressants or other immune-modifying drugs within six months prior to the first vaccination. This includes any dose level of oral steroids or inhaled steroids, but not topical steroids
  9. Subjects will be excluded if AST > 40 IU/L, ALT > 41 IU/L,  $\gamma$  GT > 71 IU/L, Total Bilirubin > 1.2 mg/ dL, Indirect Bilirubin > 1.2 mg/ dL, Direct Bilirubin > 0.4 mg/dL, Serum Creatinine > 1.2 mg/ dL (Appendix B and B-1).
  10. Subjects will be excluded in case of out of range values for the following parameters: Hemoglobin 13 to 18 g/ dL, RBC count  $4.0$  to  $7.0 \times 10^6/\mu\text{L}$  TLC  $4.0$  to  $11.0 \times 10^3/\mu\text{L}$ , platelet count 150 to  $500 \times 10^3/\mu\text{L}$ , Neutrophils 40 to 75 % or Eosinophils > 10 %, Sodium 136 to 145 mEq/L, Potassium 3.5 to 5.1 mEq/L, Random Blood Glucose 45 to 130 mg/dl and Alkaline Phosphatase 40 to 129 U/L (Appendix B and B-1)
  11. Subjects with other clinically significant abnormal laboratory values based on the normal reference range (Refer Appendix B and B1) apart from the laboratory parameters listed above.
-

- 
12. Subject with positive HIV, HBV or HCV test
  13. Subject with positive direct Coomb's test
  14. Subject with a peripheral blood film/smear with features of haemolysis or any other haematological disorder
  15. Subject unable to give written informed consent

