***Following are the footnotes for TABLE 1: PROTOCOL JAIVAC-1\_1\_09 - SCHEDULE OF VISITS AND PROCEDURES***

1. **Window Period:** A window period of specific number of days has been assigned for each visit. (*Refer Table 1 for details*). In case a subject cannot come on a scheduled day he can be called anytime in the window period for that particular visit but for subsequent visits he should be urged to adhere to the original visit schedule.
2. **Study Period:** The study consists of four (4) distinct study periods: A pre-screening period of 7 days, a screening period of 14 days, a vaccination period of 180 days and a follow-up period till 365 days from the first dose of the assigned study vaccines.
3. **Informed Consent:** There are two (2) discreet informed consent documents for this study. Following the signing of the pre-screening informed consent, blood sample for testing for anti-malarial antibodies will be taken. Only if the subject tests negative for anti-malarial antibodies, he will be administered the main informed consent form. Following the signing of the main informed consent, further study-related procedures will be undertaken.
4. **Screening number:** Following the signing of the pre-screening informed consent, each subject will be assigned a unique screening number. This same number will be used to identify the subject both during the pre-screening as well as the screening period.
5. **Demographics:** At the pre-screening Visit (Visit 1), each subject shall be required to provide demographic information (including date of birth, height, weight, gender, and race).
6. **ELISA for Anti-malarial Antibodies:** Blood sample drawn in the pre-screening period will be used for ELISA test for anti-malarial antibodies. Subjects with evidence of IgG antibodies against PfMSP-119 and PfF2 as measured by ELISA at pre-screening visit (Visit 1) will be not be further considered for the study.
7. **Vital Signs and 12-lead ECG:** General examination including vital signs i.e. temperature, pulse, respiratory rate (TPR) and blood pressure (supine BP) will be performed at every visit. One 12-lead ECG and one X-Ray Chest will be done at the screening visit (Visit 2).
8. **Birth Control Counselling:** The importance of strict adherence to the birth control measures during the study duration will be emphasised at these visits to the subjects.

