### **Seroprevalence Studies**

A study to determine prevalence rates of antibodies against *P. falciparum* antigens PfF2 and PfMSP-119 was conducted in residents of Ahmedabad and Mumbai. Hundred individuals from both sites were tested for the presence of serum antibodies against PfF2 and PfMSP-119. In Ahmedabad, 28% were seropositive for PfF2 and 10% were seropositive for PfMSP-119. Three percent were seropositive for both the antigens. Sixty five out of 100 were sero-negative for both antigens. In Mumbai, 19% were seropositive for PfF2 and 15% seropositive for PfMSP-119. Five percent were seropositive for both antigens. Seventy one out of 100 were sero-negative for both antigens (9).

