#### 5.4.2 Exclusion Criteria

*The subjects will be excluded from study entry, if any one or more of the following criteria exist at the time of the Screening/Baseline Visit:*

1. Subject with evidence of IgG antibodies against PfMSP-119 and Pff2 as measured by ELISA
2. Subject with prior history of immunisation with Hepatitis B vaccine
3. Subject with known history of malaria
4. Subject with history of allergic reactions, hypersensitivity or anaphylaxis to any of the components of the study vaccines (JAIVAC-1 – Montanide ISA 720 malaria vaccine or Hepatitis B vaccine) (including adjuvant or peptide) or with history of serious allergic reactions to any substance, requiring hospitalisation or emergency medical care
5. Subject with previous vaccination with any other malaria candidate vaccines
6. Subject with use of an investigational or non-registered drug or vaccine other than the study vaccines within three (3) months preceding the first study vaccination, or planned use during the entire clinical trial period
7. Subject, who receives any vaccination or gamma globulin during the three-month period prior to the first vaccination
8. Subject with chronic administration (defined as more than 14 days) of immuno-suppressants or other immune-modifying drugs within six months prior to the first vaccination. This includes any dose level of oral steroids or inhaled steroids, but not topical steroids
9. Subjects will be excluded if AST > 40 IU/L, ALT > 41 IU/L,  $\gamma$  GT > 71 IU/L, Total Bilirubin > 1.2 mg/ dL, Indirect Bilirubin > 1.2 mg/ dL, Direct Bilirubin > 0.4 mg/dL, Serum Creatinine > 1.2 mg/ dL (Appendix B and B-1).
10. Subjects will be excluded in case of out of range values for the following parameters: Hemoglobin 13 to 18 g/ dL, RBC count  $4.0$  to  $7.0 \times 10^6/\mu\text{L}$  TLC  $4.0$  to  $11.0 \times$

*Information contained in this publication is the property of EVI and ICGEB and is confidential and will not be disclosed to third parties without written authorization from EVI and ICGEB. No part of this document may be reproduced, stored in a retrieval system or transmitted in any form or by any means -electronic, mechanical, recording or otherwise - without the prior authorization of EVI and ICGEB*

[figure not shown][figure not shown]

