### **ELISA for anti-malarial antibodies**

During pre-screening period (D-21 through D-15), a blood sample will be collected for assessment of anti-malarial antibody titres by ELISA. Subjects without evidence of IgG antibodies against PfMSP-119 and PfF2 as measured by ELISA will be further administered the main informed consent.

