#### ***11.5.1.4 Analysis of Immunogenicity***

Immunogenicity endpoints will be analysed at Day 28 and Day 56 compared to baseline (Day 0), and Day 56 compared to Day 28 to define the primary response to the vaccine, at Day 208 compared to Day 56 to describe the antibody levels in response to the booster dose and further at Day 180 compared to Day 56 to describe the antibody persistence of the primary vaccination, and Day 365 compared to Day 208 to describe the antibody persistence. GMTs and GMCs will be presented along with 95% Confidence Intervals.

A vaccine responder will be defined as a subject with sera reactivity by ELISA against both antigens (PfMSP-119 and PfF2) greater than background reactivity (average plus three standard deviations) of pre-vaccinated sera (17).

*Information contained in this publication is the property of EVI and ICGEB and is confidential and will not be disclosed to third parties without written authorization from EVI and ICGEB. No part of this document may be reproduced, stored in a retrieval system or transmitted in any form or by any means -electronic, mechanical, recording or otherwise - without the prior authorization of EVI and ICGEB*

[figure not shown][figure not shown]

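### The responder cut-off does not say whose pre-vaccination sera form the background, and the eligibility text conflicts on whether men seropositive to one antigen may enter; if they do, pooling their sera raises the cut-off

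*Supplement*

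**What the plan says.** **Responder rule (11.5.1.4, Analysis of Immunogenicity).** "A vaccine responder will be defined as a subject with sera reactivity by ELISA against both antigens", with the limit for each being "greater than background reactivity (average plus three standard deviations) of pre-vaccinated sera". The section does not state which subjects' sera are used, whether the sample is the pre-screening one (Visit 1) or Day 0, on which scale the average and SD are taken, or whether sera already positive at baseline are left out. It names no visit for responder status.

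**Who may enter.** Two sets of passages point in different directions:

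- Exclusion criterion 1, in section 5.4.2, reads "Subject with evidence of IgG antibodies against PfMSP-1 19 and Pff2 as measured by ELISA". The synopsis has the same conjunction, and so does footnote 6 to Tables 1 and 7. Read literally, a man is excluded only if he is positive to both antigens.
- Footnote 3 to Table 1 states: "Only if the subject tests negative for anti-malarial antibodies, he will be administered the main informed consent form". Sections 6.4.1 and 7.1 and footnote 3 to Table 7 repeat this. Section 7.4.2 says: "Subjects without evidence of IgG antibodies against PfMSP-1 19 and PfF2 as measured by ELISA will be further administered the main informed consent". The natural reading is that a positive result to either antigen stops entry.

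**Prior exposure (section 2.4, Seroprevalence Studies).** "In Mumbai, 19% were seropositive for PfF2 and 15% seropositive for" PfMSP-1(19), with 5% positive to both. "In Ahmedabad, 28% were seropositive for PfF2 and 10% were seropositive for" PfMSP-1(19), with 3% positive to both.

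**The concern.** A mean + 3 SD limit is meant to describe assay background in people without specific antibody. If some contributing sera already carry antibody, both the mean and the SD rise, and the limit partly measures past exposure among those enrolled. A vaccinee with a genuine but modest rise may then fall below it, and because both antigens must be exceeded, the loss is compounded.

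There is an error in the other direction too. A man positive to one antigen before vaccination may already exceed that antigen's limit, and then needs a response only to the other.

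The responder proportion is the one responder criterion that the protocol defines. With 10 vaccinees per dosage, moving one or two men across the line changes the reported rate by 10 to 20 percentage points.

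**Working it through.** **Step 1. The survey's own figures.** Men negative to both antigens, out of 100 per city:

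- Ahmedabad: 100 − (28 + 10 − 3) = 65, as stated.
- Mumbai: 100 − (19 + 15 − 5) = 71, as stated.

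**Step 2. Who enters if only double-positives are excluded.**

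| | Admitted of 100 | Single-positive | PfF2-positive | PfMSP-1(19)-positive |
|---|---|---|---|---|
| Ahmedabad | 97 | 32/97 = 33.0% | 25/97 = 25.8% | 7/97 = 7.2% |
| Mumbai | 95 | 24/95 = 25.3% | 14/95 = 14.7% | 10/95 = 10.5% |

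Of 45 subjects, that is about 11 to 15 single-positives: 7 to 12 positive for PfF2 and 3 to 5 for PfMSP-1(19). If a positive result to either antigen excludes, all of these are zero.

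**Step 3. Effect of pooling on the cut-off.** The documents give no antibody distribution, so the following are assumptions: negative sera lognormal with median 1 and ln SD 0.5; positive sera the same shape but *f* times higher; share positive *p*.

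- Mean = 1.133 × (1 − p + p·f), where 1.133 = exp(0.5²/2).
- Second moment = 1.649 × (1 − p + p·f²), where 1.649 = exp(2 × 0.5²).
- Clean sera (p = 0): SD = √(1.649 − 1.133²) = 0.604; cut-off = 1.133 + 3 × 0.604 = 2.94.
- Example, PfF2 at Ahmedabad rates, f = 5: mean 2.30, second moment 11.85, SD 2.56; cut-off = 2.30 + 3 × 2.56 = 9.98.

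For f = 3, 5 and 10 the PfF2 cut-offs are 5.1, 8.0 and 15.6 (Mumbai) and 6.1, 10.0 and 20.1 (Ahmedabad).

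A second model in SD units of negative sera agrees in direction. With positive sera shifted by D, the cut-off is p·D + 3√(1 + p(1 − p)D²). For D = 4 to 10 the PfF2 limit rises from 3 to 5.8-12.5 (Mumbai) or 7.1-16.0 (Ahmedabad). Simulation with 45 sera gave a median limit of 2.97 when none were positive.

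**Step 4. Effect on responders.** Further assumptions: post-dose geometric mean R times the negative median for each antigen, ln SD 0.8, antigens independent. P(above limit c) = Φ(ln(R/c)/0.8), multiplied over the two antigens. Percentages exceeding both limits, Mumbai / Ahmedabad:

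| R | Clean background | f = 3 | f = 5 | f = 10 |
|---|---|---|---|---|
| 10 | 88 | 67 / 63 | 41 / 37 | 10 / 8 |
| 30 | about 100 | 98 / 97 | 92 / 89 | 67 / 61 |
| 50 | about 100 | about 100 / about 100 | 98 / 97 | 88 / 85 |

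At R = 100 every entry is at least 97%. The loss is large when the vaccine response is close to the level of naturally positive sera, and small when it is well above.

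**Step 5. The upward error.** With f = 5, the share of positive sera already above the clean limit before any dose is 1 − Φ(ln(2.94/5)/0.5) = 86%. A clean background therefore does not mend this error; a fold rise over the subject's own baseline is needed as well.

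**Step 6. Log scale.** With clean sera, mean + 3 SD of the logs gives exp(3 × 0.5) = 4.48 against 2.94. At R = 10, responders to both fall from 88% to 71%. Changing the scale is a separate choice and makes the rule stricter.

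**The case against.** A reader might infer that the plan computes the cut-off from all baseline sera on the raw scale, that single-positives will certainly be enrolled, and that the responder rate is therefore biased sharply downward. The documents do not support that reading.

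- Section 11.5.1.4 says neither all sera nor raw scale; it is silent on both.
- The procedure before main consent admits only men who test negative, and under that rule there are no single-positives to contaminate the background. Men with a known history of malaria are also excluded, which the survey figures do not reflect, and the survey covers only Mumbai and Ahmedabad.
- The lowest responder rates in the table rest on an assumed tenfold response. No response size is stated in the documents.
- The bias is not one-directional, as Step 5 shows.
- Analysis is descriptive, with no hypothesis. ELISA levels are also reported as geometric means with intervals and compared with Day 0, and responder status plays no part in dose escalation.
- Section 11 promises a separate SAP, which is not shown and may define the background sera.

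These points limit the size and certainty of the problem. Two things still stand. The numbered exclusion criterion contradicts the consent procedure, and membership of the per-protocol set depends on meeting the numbered criteria. And the protocol already fixes a responder rule that, followed as worded, would allow positive sera into the background.

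**Conclusion.** The point holds conditionally. The background set is undefined and the eligibility passages conflict. If single-positives enter and their sera are pooled, the PfF2 limit rises from about 2.9 to between 5 and 20 times the negative median under the lognormal assumptions with f = 3 to 10. Weak or moderate responders are then lost: from 88% to between 8% and 67% at a tenfold response, but only to 89-92% at a thirtyfold response with f = 5. Some men positive at baseline can be misclassified in the other direction. If single-positives are excluded, the inflation is essentially nil.

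The prevalence shares follow from the protocol's survey. The antibody levels, spreads, independence and response sizes are assumptions. The result affected is a secondary, descriptive one, so this should be corrected but does not threaten the primary safety objective.

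**What to change.** 1. Reconcile exclusion criterion 1 (section 5.4.2 and synopsis) and footnote 6 to Tables 1 and 7 with the pre-screening procedure in footnote 3 and sections 6.4.1, 7.1 and 7.4.2, so that all state the same rule on positivity to one antigen.
2. In section 11.5.1.4 or the SAP, compute the cut-off separately for each antigen from Day 0 sera of subjects negative for that antigen at pre-screening. This works under either eligibility rule.
3. Report responders for each antigen and for both, separately at Days 28, 56, 180, 208 and 365, beside the fold rise over the subject's own Day 0 value.
4. State the scale. A log-scale limit may be shown as a sensitivity analysis, noting that it is stricter (about 4.5 against 2.9 times the negative median at an assumed ln SD of 0.5).

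The cost is wording only, since pre-screening and Day 0 ELISA are already scheduled. The one drawback is a slight departure from the published rule that the protocol cites, which can be kept as a sensitivity analysis. The definition should be settled before the ELISA data are analysed, including for the interim analysis after the third dose.

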## 12 REGULATORY AND ETHICAL REQUIREMENTS

This clinical study is designed and shall be implemented and reported in accordance with the ICH Harmonised Tripartite Guidelines for Good Clinical Practice (ICH-GCP), the ethical principles laid down in the Declaration of Helsinki and as per the applicable local regulations of the country where the study takes place.

### 12.1 Regulatory Authority Approval

Regulatory notification for this study will be sent to the responsible authority, the DCGI, according to the applicable country-specific laws and regulations of India. DiagnoSearch Life Sciences (DLS) will obtain the necessary approval from the DCGI on behalf of the Sponsor (EVI/ICGEB) prior to initiation of the study.

### 12.2 Institutional Review Boards/Ethics Committees

#### 12.2.1 Institutional Review Board

The Sponsor's Institutional Review Board (ICGEB-IRB) will review and give approval to the present study protocol before its implementation by the study site.

#### 12.2.2 Independent Ethics Committees

Study-related documents (including the protocol, subject information sheet, informed consent form or any other relevant document must be reviewed and approved by a properly constituted IRB/IEC/Research Ethics Board before study start. It is the investigator's responsibility to ensure that this protocol is reviewed and approved by the local IEC responsible for the study site. Where necessary, the sponsors will provide summaries of toxicological, clinical and pharmacological data to support this application. The IEC must also review and approve the Subject Information Sheet, Informed Consent Form and any other written information to be provided to the subject.

Written IEC approval shall be obtained and sent by the Investigator or his/her designee to the Sponsor prior to the start of the study. The IEC approval letter must identify all documents approved and list the study site, the study investigator, protocol number, date, version and title, Subject Information Sheet and Informed Consent Form number, date and version and the date of IEC approval. A list of IEC members shall be attached to the approval letter.

No deviations from, or changes to, the protocol shall be implemented without prior written IRB/IEC approvals of an appropriate amendment, except when necessary to eliminate immediate hazards to the subjects or when the change(s) involves only logistical or administrative aspects of the study (e.g., change of monitor(s), telephone number(s)). The investigator shall provide to the sponsors a statement from the IEC confirming the IEC is organised and operates according to ICH-GCP and applicable laws and regulations.

Prior to submitting to the IEC/IRB, the investigator is also required to sign a protocol signature page confirming his/her agreement to conduct the study in accordance with these documents and all of the instructions and procedures found in this protocol and to give access to all relevant data and records to monitors, auditors, Clinical Quality Assurance representatives, designated agents of, IRBs/IECs, and regulatory authorities as required. If an inspection of the clinical site is requested

*Information contained in this publication is the property of EVI and ICGEB and is confidential and will not be disclosed to third parties without written authorization from EVI and ICGEB. No part of this document may be reproduced, stored in a retrieval system or transmitted in any form or by any means -electronic, mechanical, recording or otherwise - without the prior authorization of EVI and ICGEB*

[figure not shown][figure not shown]

by a regulatory authority, the investigator must inform immediately that this request has been made.

### 12.3 Subject Information and Informed Consent

There are two (2) discreet informed consent documents for this study. Following the signing of the pre-screening informed consent form, the pre-screening blood sample for testing for anti-malarial antibodies will be drawn. Eligible subjects may only be included in the study after providing written (witnessed, where required by law or regulation), IRB/IEC-approved informed consent in a language understood by the subject. Following the signing of the main informed consent for the actual study participation, the relevant study related activities and screening procedures (i.e., all of the procedures described in the protocol) will be undertaken. The process of obtaining informed consent (both pre-screening and main consent) will be documented in the subject's source documents.

The Sponsor or its designee will provide the proposed informed consent forms that comply with the ICH-GCP guideline and regulatory requirements and are considered appropriate for this study to the study investigator in two separate documents. Any changes to the proposed consent form suggested by the investigator must be agreed to by the Sponsor before submission to the IRB/IEC, and a copy of the final approved version must be provided to the study monitor after IRB/IEC approval.

The investigator or his/her designee will inform the subject of all aspects pertaining to the subject's participation in the study. The process for obtaining subject informed consent will be in accordance with all applicable regulatory requirements. Prior to including any subject in the clinical study, his/her free and expressed informed consent must be obtained in writing. The written informed consent must be signed and dated by both the investigator and his/her designee and the subject prior to any study related procedure. The investigator or his/her designee will describe the study protocol to potential subjects. The Subject Information Sheet and the Informed Consent Form may be given to the subject or read to him. The investigator must give the subjects ample opportunity to inquire about details of the study and ask any questions before dating and signing the Informed Consent Form.

Original subject's signed informed consent forms must be kept on file by the investigator for possible inspection by regulatory authorities and Sponsor (or its designees). The subject must receive a copy of the signed and dated informed consent form, and any subsequent updates or amendments. The study monitor will check the documentation of the individual Informed Consent Form during each monitoring visit.

